### Inclusion criteria

Being aged 18–75 yearsHaving an Eastern Cooperative Oncology Group performance status of 0-2Having histologically proven ESCCHaving a pretreatment stage of cT2N0M0-cTxNxM1a-1b (according to the 6th edition of AJCC/UICC TNM staging system, excluding metastasis beyond the supraclavicular or celiac lymph node and distant organ metastasis)Surgically unresectable.Not having prior chemotherapy or radiotherapy history and not being enrolled in other clinical trialsHaving adequate organ function (white blood cell count ≥ 3 × 10^9^/L; neutrophil count ≥ 1.5 × 10^9^/L; hemoglobin level ≥ 90g/L; platelet count ≥ 100 × 10^9^/L; total bilirubin level ≤ 1.5 × upper limit of normal (ULN); aspartate transaminase level ≤ 2.5 × ULN; alanine transaminase level ≤ 2.5 × ULN; serum creatinine level ≤ 1.5 × ULN)Having a life expectancy of ≥3 monthsProviding written informed consent.

### Exclusion criteria

Having a past or current history of another malignant disease, except completely treatable nonmelanoma skin cancer and cervical carcinoma in situ (with PFS ≥ 3 years).Having an uncontrolled cardiac disease (e.g., myocardial infarction within the previous 6 months and coronary artery disease), diabetes, or hypertension.Having a severe mental disorderBeing pregnant or lactatingHaving a tumor invading the airway or aortaHaving complete obstruction due to esophageal cancer, signs of esophageal perforation or bleeding, or already developing perforation and bleedingReceiving oral or intravenous corticosteroidsHaving dysfunction in major organs, such as the liver, kidneys, heart, and lungs, immune deficiency, or active infectionHaving other possibly ineligible conditions based on the researchers’ judgment

### Exit criteria

Cancer progressionRequest to withdraw from the trialDevelopment of grade 4 or higher nonhematologic toxicity (according to Common Terminology Criteria for Adverse Events (CTCAE; version 4.0), which could not reduce grade 2 or after treatment) or development of serious adverse events.Interruption in radiotherapy for >2 weeks for any reasonsNo treatment initiation for 4 weeks after enrollmentDevelopment of possibly ineligible conditions based on the researchers’ judgment

### Study interventions

#### Chemotherapy

CCRT (Both arms)

All patients will receive two cycles of chemotherapy (cisplatin: 75 mg/m^2^/day, IVGTT, day 1; capecitabine: 800 mg/m^2^/day, bid, PO, d1–14) every 3 weeks during radiotherapy.

Consolidation chemotherapy (Arm A)

After CCRT, patients in arm A will receive two cycles of consolidation chemotherapy (cisplatin: 75 mg/m^2^/day, IVGTT, day 1; capecitabine: 1000 mg/m^2^/day, bid, PO, d1–14) every 3 weeks.

Observation group (Arm B)

Patients in arm B will receive no interventions.

#### Radiotherapy

The treatment plan is shown in Fig. 1. Radiation will be delivered with ≥6-MV photons 5 days per week to administer a total dose of 59.4 Gy in 33 fractions. All patients will be placed in the treatment position in an individualized immobilization device, and IMRT will be used.

The definition of volumes will be in accordance with the Report 50 (1993) and Report 62 (1999) of the International Commission on Radiation Units & Measurements (ICRU). The gross target volume (GTV) is defined as the gross demonstrable location and extent of the tumor, detected through endoscopic ultrasound, barium swallow x-ray, or computed tomography (CT) (whichever is larger). A regional lymph node with a diameter of ≥1 cm (for cervical, mediastinal, or celiac lymph nodes) or 0.5 cm (for tracheoesophageal groove lymph nodes) or that proven to be metastatic through positron emission tomography (PET)–CT will be defined as a GTVnd. Involved-field irradiation will be adopted when defining the clinical target volume (CTV). The CTV encompasses the GTV and the region draining the lymphatics, which will be defined as follows: a 3-cm craniocaudal margin, a 0.5–0.8-cm lateral margin beyond the GTV, and a GTVnd with a 1–1.5cm margin, including the metastatic lymph nodes. The PGTV is at 1 cm craniocaudally beyond the GTV and 0.5cm radially and the GTVnd. The planning target volume (PTV) will be defined as the CTV plus a 0.5–0.7cm expansion. Patients will be treated typically with daily fractions of 1.8 Gy to a total initial dose of 50.4 Gy to the PTV, followed by a cone down of 9 Gy to a total dose of 59.4 Gy to the PGTV.

The treatment plan will consider normal organ dose constraints as follows: The volume of lung tissue receiving ≥20 Gy should be <28% of the total lung volume, and the mean dose has to be <18 Gy. For the spinal cord, the maximal point dose should be <45 Gy. The volume of the heart receiving ≥30 Gy radiation must be <40% of the total heart volume, and the mean dose should be <26 Gy. The PTV and the organ at risk will be assessed using a dose–volume histogram.

### Dose modifications

#### Radiotherapy interruption

In patients who develop grade 3 or higher hematological or nonhematological toxicity, radiotherapy will be delayed until the toxicity grade decreases to ≤2. At most, a 2-week delay will be permitted. Patients with a longer delay will be excluded from the trial.

#### Chemotherapy interruption

Chemotherapy dose modifications will be based on the most severe toxicity in the patients' last cycle. In patients who develop grade 2 or higher hematological toxicity, chemotherapy will be delayed until the toxicity grade decreases to ≤1. At most, a 2-week delay will be permitted. Patients with a longer delay will be excluded from the trial and asked to discontinue chemotherapy.

Chemotherapy dose modifications may be required in the following situation: a patient develops grade 4 hematological toxicity or grade 3 or higher nonhematological toxicity, but the toxicity grade decreases to ≤1 within 2 weeks before the next cycle. Patients who remain ineligible after this period will be asked to discontinue chemotherapy.

If modification is necessary, cisplatin and capecitabine doses will be reduced to 75% of the planned dose. Dose modifications may be made at most twice; if more than two modifications are required, chemotherapy will be terminated.

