### Study objectives

The main objective of this trial is to compare OS in ESCC patients treated with or without consolidation chemotherapy after dCCRT. Our secondary objectives are to compare PFS, locoregional PFS (LPFS), distant metastasis-free survival (DMFS), and treatment-related toxicity.

OS is defined as the time from the date of dCCRT initiation until the date of death. PFS is defined as the time from the date of dCCRT until the date of first progression or death. LPFS is defined as the time from the date of dCCRT until the date of first locoregional progression (a primary tumor or locoregional lymph nodes) or death. DMFS is defined as the time from the date of dCCRT until the date of first distant metastasis (nonregional lymph nodes or a distant organ) or death.

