### Assessments during the follow-up phase

After completion of the study treatment, patients will be followed up every 3 months for the first 2 years and then every 6 months from the third year onward. All patients will be followed up until death or at least 3 years after treatment.

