### Statistical analysis

Data analyses will be performed according to the intention-to-treat principle in all randomized patients. Between-group comparisons will be performed using chi-squared and Fisher’s exact test for categorical parameters and Student’s *t* test for normally distributed continuous variables or the Mann–Whitney *U* test or analysis of variance for nonnormally distributed continuous variables. Survival rates will be calculated using the Kaplan-Meier method, and comparisons between the groups will be performed using the log-rank test. The difference will be considered statistically significant at a *P* value of <0.05.

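### For randomised patients, trial exits for progression, serious adverse events and chemotherapy delay contradict the planned intention-to-treat analysis and survival follow-up

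*Protocol article*

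**What the plan says.** Five parts of the protocol article bear on this.

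- **Exit criteria.** The list (its items run together in the extracted text) opens "Cancer progressionRequest to withdraw from the trialDevelopment of grade 4 or higher nonhematologic toxicity" and continues "or development of serious adverse events". No item is limited to the time before randomisation or to study treatment.
- **Chemotherapy interruption.** After a delay of more than 2 weeks: "Patients with a longer delay will be excluded from the trial and asked to discontinue chemotherapy". For toxicity that does not resolve in time, the same section says only: "Patients who remain ineligible after this period will be asked to discontinue chemotherapy".
- **Radiotherapy interruption.** "Patients with a longer delay will be excluded from the trial".
- **Assessments during the follow-up phase.** "All patients will be followed up until death or at least 3 years after treatment".
- **Statistical analysis and Study objectives.** "Data analyses will be performed according to the intention-to-treat principle in all randomized patients". The primary endpoint runs to death: "OS is defined as the time from the date of dCCRT initiation until the date of death".

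Two further facts fix the timing. Under Assessments during the treatment phase, patients free of progression are randomised in a window of 2 to 6 weeks, which I read as counted from the end of dCCRT; those with progression are excluded. Under Study interventions, only Arm A then receives chemotherapy.

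**The concern.** A randomised patient cannot both leave the trial at progression and be followed until death. Nor can a patient excluded after a treatment delay be in an analysis of all randomised patients, unless exclusion means something other than what it says. The article nowhere states that exited patients stay in follow-up.

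This is a non-inferiority trial with OS as primary endpoint. Most deaths in this disease can be expected to follow progression, so a site that closes a patient's record at progression loses the events the trial is built on. Two secondary endpoints are exposed as well. LPFS needs observation after a first distant failure, and DMFS needs it after a first locoregional failure.

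**Working it through.** **1. Which removals conflict with intention-to-treat**

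| Rule | When it can act | Conflict |
|---|---|---|
| Radiotherapy interrupted more than 2 weeks | During dCCRT, before randomisation | None |
| Treatment not started within 4 weeks of enrolment | Before randomisation | None |
| Chemotherapy delay in the concurrent cycles | Before randomisation | None |
| Progression found before randomisation | Before randomisation | None |
| Chemotherapy delay in the consolidation cycles | After randomisation, Arm A only | Yes |
| Progression after randomisation | Both arms | Yes |
| Serious adverse event after randomisation | Both arms | Yes |

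**2. Size if observation ends at progression**

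The article gives no progression or post-progression rates, so this is an illustration. Arm A's 2-year OS of 60% comes from the sample size section. Arm B at 45% is 60% minus the 15-point margin; it lies below the article's assumed range of 48%–65% and marks the non-inferiority limit. Assumptions:

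- death without progression μ = 0.004 per month in both arms;
- median survival after progression 9 months, so ν = ln 2 / 9 = 0.0770 per month;
- progression λ = 0.0364 (A) and 0.0681 (B) per month.

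True survival: S(24) = e^(−(λ+μ)·24) + [λ/(ν−λ−μ)]·[e^(−(λ+μ)·24) − e^(−ν·24)].

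- A: 0.379 + 0.994 × (0.379 − 0.157) = 0.600
- B: 0.177 + 13.85 × (0.1772 − 0.1575) = 0.450

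If every patient leaves at progression, Kaplan-Meier sees only deaths without progression and estimates e^(−0.004×24) = 0.908 in **both** arms. The 15-point deficit shows as 0. The share of 2-year deaths still observed is:

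- A: (0.004/0.0404) × (1 − 0.379) = 0.061, out of 0.400, or 15%
- B: (0.004/0.0721) × (1 − 0.177) = 0.046, out of 0.550, or 8%

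A simulation with other assumptions (μ = 0.003, median PFS 12 to 24 months) gives the same picture: about 93% in both arms, and 7%–13% of deaths observed.

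If only a fraction f of patients is lost at progression, at random and equally in both arms, Kaplan-Meier estimates exp(−∫h dt) with h = [μF + (1−f)νP]/[F + (1−f)P]. Here F is the probability of being alive without progression and P of being alive after it. With the inputs above:

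| Lost at progression | 2-year OS, A | 2-year OS, B | Difference (points) |
|---|---|---|---|
| 0% | 60.0% | 45.0% | 14.9 |
| 25% | 65.0% | 50.0% | 15.0 |
| 50% | 71.3% | 57.3% | 14.0 |
| 75% | 79.6% | 69.0% | 10.6 |
| 100% | 90.8% | 90.8% | 0.0 |

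The absolute rates are inflated at once. The difference erodes mainly when most progressing patients are lost, which is what a rule applied to everyone produces.

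**3. Size of the chemotherapy-delay exclusion**

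If a fraction x of Arm A is dropped and has 2-year OS s, the retained patients show (0.60 − x·s)/(1 − x).

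- Smallest effect, x = 5%, s = 50%: (0.60 − 0.025)/0.95 = 0.605, a shift of +0.5 points
- Middle, x = 10%, s = 40%: (0.60 − 0.040)/0.90 = 0.622, a shift of +2.2 points
- Largest, x = 15%, s = 30%: (0.60 − 0.045)/0.85 = 0.653, a shift of +5.3 points

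This flatters Arm A, so it works against showing Arm B non-inferior. The values of x and s are assumed.

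**The case against.** The strongest reply is that exit means only leaving protocol treatment. The follow-up and analysis sections already set the governing rules, no section says survival follow-up stops at exit, and a condensed article often leaves the off-treatment/off-study distinction to the full protocol. If that is what is meant, there is no bias.

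The printed words point the other way. Under Chemotherapy interruption, exclusion from the trial is added to stopping chemotherapy, and the same section has separate wording for stopping treatment alone. The exit list puts progression next to a request to withdraw from the trial. An Arm B patient who progresses after randomisation has no study treatment left to stop. This is therefore a contradiction in the text rather than a missing detail.

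Several stronger readings are tempting but not supported:

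- *Every removal breaches intention-to-treat.* Those before randomisation do not.
- *Most toxicity exits fall in Arm A.* Only the chemotherapy-delay rule is specific to Arm A after randomisation. The toxicity and serious-adverse-event exits are not tied to chemotherapy, and both arms have had chemoradiotherapy.
- *Everything pushes towards non-inferiority.* The two mechanisms run in opposite directions.
- *A 15-point deficit would in practice vanish.* The zero follows from total loss at progression and equal progression-free death hazards. It is a worst case and not a forecast.
- *The toxicity rules clash throughout.* The grade-based exit concerns toxicity that does not resolve and dose modification concerns toxicity that does, so these are compatible. Only the unqualified serious-adverse-event exit sits badly with continuing on modified doses.

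**Conclusion.** The point stands for randomised patients and is worth fixing before further follow-up accrues. As written, the exits for progression and serious adverse events, and the exclusion after a delay in consolidation chemotherapy, contradict the intention-to-treat population, the follow-up rule and the primary endpoint.

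The consequence depends on how sites apply the wording. Carried out literally, exit at progression would leave most deaths unobserved: only 8%–15% of 2-year deaths are seen in the main illustration. It would bias towards non-inferiority by anything up to the whole 15-point margin, while partial loss at random does much less. The Arm A-only exclusion moves the comparison the other way by about 0.5 to 5 points. The two need not cancel. The documents do not show that patients have actually been lost in this way, so it cannot be said that the randomised comparison has been destroyed.

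**What to change.** Split the exit criteria at randomisation.

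- **Before randomisation:** patients may be excluded from the trial as now. The radiotherapy interruption section needs no change on this account.
- **After randomisation:** where progression, toxicity, a serious adverse event or a chemotherapy delay ends anything, it ends protocol treatment only. Under Chemotherapy interruption, for randomised patients, replace exclusion from the trial with: discontinues protocol treatment, remains in follow-up and in the intention-to-treat analysis.
- **Follow-up:** state that survival follow-up continues after these events, that LPFS and DMFS events are still collected after a first progression of the other type, and that only withdrawal of consent to follow-up ends observation.
- **Reconcile** the unqualified serious-adverse-event exit with the section that keeps patients on modified doses. No clinical threshold needs to change for this point, and none is proposed.

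Retitling the whole exit list as treatment discontinuation would not work. It would mislabel withdrawal requests, non-initiation and the exclusion of patients who progress before randomisation.

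The cost is an amendment to the wording and survival contacts that the follow-up section already promises. The article reports 200 patients recruited, so survival status must also be obtained for any of them who were randomised and have already exited.

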### Study objectives

The main objective of this trial is to compare OS in ESCC patients treated with or without consolidation chemotherapy after dCCRT. Our secondary objectives are to compare PFS, locoregional PFS (LPFS), distant metastasis-free survival (DMFS), and treatment-related toxicity.

OS is defined as the time from the date of dCCRT initiation until the date of death. PFS is defined as the time from the date of dCCRT until the date of first progression or death. LPFS is defined as the time from the date of dCCRT until the date of first locoregional progression (a primary tumor or locoregional lymph nodes) or death. DMFS is defined as the time from the date of dCCRT until the date of first distant metastasis (nonregional lymph nodes or a distant organ) or death.

### Pretherapeutic assessments

Before administering any treatment, we will perform routine examination and record its results for every potential patient. The routine examination will include the following:A physical examination, as well as vital sign and medical history takingKarnofsky performance status and Eastern Cooperative Oncology Group performance statusStandard laboratory tests (routine complete blood count and blood biochemistry), pulmonary function test, and electrocardiographyUpper digestive tract endoscopy with biopsyCT of the thorax or PET–CT; magnetic resonance imaging (MRI) of the esophagus, endoscopic ultrasound of the esophagus, or both; brain MRI (if needed); whole-body bone emission CT (if required); or CT or ultrasound of the neck and abdomenEuropean Organisation for Research and Treatment of Cancer quality of life

### Assessments during the treatment phase

The outcomes of physical examinations, vital signs, routine complete blood count, blood biochemistry, and radiotherapy-related pulmonary and esophageal toxicity will be recorded weekly during the dCCRT period, according to CTCAE (version 4.0). Changes in esophageal wall thickness and lymph node size (if needed) will be evaluated through contrast-enhanced CT of the neck, thorax, and abdomen. Changes in the esophageal tract will be assessed through contrast-enhanced CT of the upper gastrointestinal tract. The residual primary tumor will be evaluated through upper endoscopy followed by biopsy. Local tumors, locoregional lymph nodes, and distant metastases will be assessed through PET–CT. After 2–6 weeks of dCCRT, patients without disease progression will be randomized at a 1:1 ratio to arm A or B by a central randomization center; moreover, patients demonstrating disease progression will be excluded from the study.

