The incidence rate of local recurrence among esophageal cancer patients who undergo dCCRT can be 43%–58%, and this recurrence can significantly reduce the patients' long-term survival rates [7–9]. Recent studies have suggested that LPFS of ESCC patients receiving dCCRT with a higher radiation dose (≥59.4Gy) and those receiving dCCRT with a standard radiation dose (50 Gy/2 Gy or 50.4 Gy/1.8 Gy) is comparable [21, 22]. The standard radiation dose for dCCRT is 50 Gy, as indicated in the RTOG 85-01 trial [5]. However, Chang et al. noted that a higher dose of radiation (≥60 Gy) may prolong survival [23]. This finding was further supported by another study [24]—which also indicated that a higher dose may enhance local control. Nevertheless, recent randomized studies have demonstrated that in dCCRT for ESCC, the standard radiation dose (50 Gy/2 Gy or 50.4 Gy/1.8 Gy) has an effect similar to that of a higher radiation dose (≥59.4 Gy/1.8 Gy) but with relatively less treatment-related toxicity [21, 22, 25, 26]. Consequently, in future clinical practice, the standard radiation dose should be recommended for dCCRT in patients with ESCC.

Although several studies have analyzed the effects of different CCRT regimens, none have demonstrated considerably improved treatment efficacy or substantially decreased toxicity [15, 16, 27–30]. 5-Fluorouracil plus cisplatin has been used as a standard regimen in many dCCRT studies after the RTOG 85-01 trial [5, 6, 31–33]. This chemotherapy regimen achieves a curative effect but with serious treatment toxicity, such as severe myelosuppression and mucositis [5]. In three trials (including the SCOPE1 trial), capecitabine, an oral prodrug of 5-fluorouracil, demonstrated a high complete remission rate with acceptable toxicity [28, 29]. Therefore, capecitabine plus cisplatin may be a more acceptable candidate for subsequent dCCRT trials [14, 34, 35]. Some trials have also explored the efficacy of other chemotherapy regimens in dCCRT, such as paclitaxel plus carboplatin and the FOLFOX regimen [15, 17, 36] and 5-fluorouracil plus paclitaxel [30]. However, none of the aforementioned regimens demonstrates relatively high efficacy or relatively less toxicity.

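### The safety endpoint counts only treatment-related toxicity in an open-label trial where one arm has no ongoing treatment, and the stated toxicity recording ends before the arms differ and names only radiotherapy-related organ effects

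*Protocol article*

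**What the plan says.** Under Study objectives, the protocol article lists the secondary comparisons: "Our secondary objectives are to compare PFS, locoregional PFS (LPFS), distant metastasis-free survival (DMFS), and treatment-related toxicity". The Abstract describes the trial as open-label.

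Under Study interventions (Chemotherapy), both arms have two cycles of cisplatin and capecitabine during radiotherapy. After that, "patients in arm A will receive two cycles of consolidation chemotherapy", while "Patients in arm B will receive no interventions".

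Under Assessments during the treatment phase, one sentence sets out what is recorded. It opens with "The outcomes of physical examinations, vital signs, routine complete blood count, blood biochemistry" and continues: "radiotherapy-related pulmonary and esophageal toxicity will be recorded weekly during the dCCRT period, according to CTCAE (version 4.0". The same section places randomization thus: "After 2–6 weeks of dCCRT, patients without disease progression will be randomized at a 1:1 ratio to arm A or B". Assessments during the follow-up phase gives visit times but does not mention toxicity.

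Two other sections act on toxicity more broadly. Chemotherapy interruption (under Dose modifications) uses the worst toxicity of the last cycle, both hematological and nonhematological. Exit criteria refers to nonhematologic toxicity of grade 4 or higher by CTCAE 4.0 and to serious adverse events.

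**The concern.** Two features of the stated safety plan fit poorly with the randomized question, which is what two extra chemotherapy cycles add and what they cost.

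The first is attribution. The endpoint counts an event only if someone judges it to be treatment-related. After randomization one arm is on chemotherapy and the other is under observation, and the investigator knows which. An event such as late anemia, fatigue or pneumonitis may be put down to current chemotherapy in Arm A and to the disease in Arm B. That would exaggerate the cost of consolidation.

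The second is the recorded set. The only organ toxicity named is radiotherapy-related and confined to lung and esophagus, and the stated window is the chemoradiotherapy period, which both arms share. Symptomatic chemotherapy toxicity elsewhere, during consolidation or observation, is not named. That would understate the cost of consolidation.

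The trial tests whether consolidation can be left out within a 15% non-inferiority margin. The article does not tie the margin to toxicity. A reader of a non-inferior result will nevertheless want to know what toxicity is spared, so the safety comparison will carry weight.

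**Working it through.** The article states no toxicity rate and no safety power, so there is no figure to reproduce. The check sets the sections side by side and then illustrates size under assumptions.

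**Does the recording match the contrast?**

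| Element | What the article fixes | Section |
|---|---|---|
| Difference between arms | Two further chemotherapy cycles against observation | Chemotherapy |
| Organ toxicity named | Radiotherapy-related, lung and esophagus | Assessments during the treatment phase |
| Also recorded | Examination, vital signs, blood count, biochemistry | Same sentence |
| Recording window | Weekly during chemoradiotherapy | Same sentence |
| Toxicity acted on | Hematological and nonhematological, no organ limit | Chemotherapy interruption; Exit criteria |
| Endpoint filter | Treatment-related | Study objectives |

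The wording on the time of randomization is loose. If it means 2 to 6 weeks after chemoradiotherapy ends, the window closes before randomization. If it means 2 to 6 weeks into a course of 33 fractions at 5 per week (33/5 = 6.6 weeks), the window runs past randomization but still closes before the treatments differ. On either reading, the events in the stated window say nothing about consolidation.

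**Attribution.** Let r be the any-cause event rate, equal in both arms, and fA and fB the shares called related. The reported rates are r × fA and r × fB, and the false difference is r × (fA − fB). All values of r, fA and fB are assumptions. With r = 20%:

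- 55% against 45%: 0.20 × 0.55 = 11% and 0.20 × 0.45 = 9%; difference 2 points.
- 70% against 30%: 14% and 6%; difference 8 points.
- 80% against 20%: 16% and 4%; difference 12 points.

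**How often would such a difference reach P < 0.05?** The calculation uses 300 per arm (600 randomized 1:1, Sample size considerations) and a two-sided 5% test of two proportions by the normal approximation, pooled variance under the null:

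power = Φ{(d − 1.96 × s0)/s1}, with s0 = √[2p̄(1 − p̄)/n] and s1 = √{[pA(1 − pA) + pB(1 − pB)]/n}.

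For 14% against 6%: s0 = √(2 × 0.10 × 0.90/300) = 0.02449; s1 = √[(0.1204 + 0.0564)/300] = 0.02428; (0.08 − 0.04801)/0.02428 = 1.32, giving 0.91.

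| r | fA v fB | Reported rates | Probability of a false significant difference |
|---|---|---|---|
| 20% | 55% v 45% | 11% v 9% | 0.13 |
| 20% | 70% v 30% | 14% v 6% | 0.91 |
| 20% | 80% v 20% | 16% v 4% | above 0.99 |
| 20% | 90% v 50% | 18% v 10% | 0.81 |
| 10% | 90% v 50% | 9% v 5% | 0.48 |
| 10% | 80% v 20% | 8% v 2% | 0.92 |

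With equal attribution the rate stays near 0.05.

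**Counting from the right time.** Suppose the true post-randomization rates are 20% and 10% (power 0.93 when compared alone). If a patient counts as having an event at any time, and a share q had one before randomization independently of the later risk, the rates become 1 − (1 − q)(1 − p):

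- q = 20%: 1 − 0.8 × 0.8 = 36% against 1 − 0.8 × 0.9 = 28%; power 0.56.
- q = 40%: 1 − 0.6 × 0.8 = 52% against 1 − 0.6 × 0.9 = 46%; power 0.31.

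Pooling shared earlier toxicity with later toxicity therefore masks a real difference.

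**The case against.** The strongest reply is that the article records more than one phrase suggests, and that much of this holds.

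A reader might infer that recording is limited to lung and esophageal events. It is not. The same sentence covers examination, vital signs, blood count and biochemistry, so hematological, renal and hepatic toxicity are within reach, and examination can reveal mucositis. The dose and exit rules cannot work unless other nonhematological toxicity is graded. So one cannot say that chemotherapy events elsewhere contribute nothing, only that the recording sentence does not name them.

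A reader might also infer that Arm B has nothing to which an event could be attributed. That is too strong: Arm B has had full chemoradiotherapy, and pneumonitis, for example, can be attributed to it in either arm. What Arm B lacks is ongoing treatment. The asymmetry is one of degree.

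The Discussion offers only modest support. Its phrase "serious treatment toxicity, such as severe myelosuppression and mucositis" describes fluorouracil with cisplatin, and it goes on to describe capecitabine's toxicity as acceptable.

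Finally, adverse-event forms and attribution procedures normally sit in the full protocol, which is not shown. Their absence is no finding here. That does not remove the point, because the article positively fixes an attribution-filtered endpoint, and a fuller document would still be applying that filter in an open-label setting.

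**Conclusion.** The point holds as a risk of bias in one secondary endpoint, and it is cheap to remove. The stated comparison depends on open-label judgments of relatedness that may differ by arm. The stated recording covers a period before the treatments diverge and names organ toxicity from the treatment that the arms share. Attribution can inflate the apparent cost of consolidation, while the recorded set, or pooling with earlier toxicity, can hide it.

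The size cannot be taken from the documents. The 2 to 12 points, and the probabilities of a false significant result, rest on assumed event rates and attribution splits and on all 600 patients being randomized. They show what is possible, not what is expected. A reader might conclude that the toxicity difference will be uninterpretable; the documents do not support that, because the extent of differential attribution and of actual recording is unknown. The primary survival endpoint is not affected.

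**What to change.** In Assessments during the treatment phase, state that CTCAE version 4.0 adverse events of any organ and any cause are recorded and graded in the same way in both arms, and that this continues through the consolidation or observation period after randomization.

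In Study objectives, make the between-arm safety endpoint the worst grade, and the proportion with grade 3 or higher, of all-cause events that arise or worsen after randomization. Keep relatedness as a descriptive column. Toxicity during chemoradiotherapy can be reported separately as a shared baseline.

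The cost is a broader adverse-event form and one more table, with no extra procedures. The downside is that disease-related events enter both arms and add some noise. The article reports 200 patients recruited, so 600 − 200 = 400 of the planned number would be recorded this way from the start. For the first 200, the report should say whether the earlier forms captured all-cause events.
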